## Sample size

### Justification for research question 1: defining the optimal dose of salbutamol

Can we define the dose of inhaled salbutamol that is appropriate for children aged 2 years 6 months old to 6 years 11 months old with recurrent wheeze?

We plan to compare the difference in change from baseline between different salbutamol doses. From the data by Beydon et al. [9], we would define the minimum clinically important difference (MCID) for paired *t* tests as mean −0.23, standard deviation (SD) 0.19, and set the threshold of significance at 0.01 to account for multiple *t* tests. In order to detect a worthwhile difference of this size between dosages with 90 % power, a minimum of 24 patients will be needed in each dosage group, giving a sample size of 96 patients.

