### Justification for research question 2: Arg versus Gly beta agonist response

Can we predict the salbutamol dose that is appropriate for an individual child using simple, non-invasive and inexpensive tests that can be performed in the outpatient setting?

The hypothesis to be tested is that children with wheeze who are either homozygous or heterozygous for arginine at position 16 of the beta2 receptor (i.e. Arg/Arg or Arg/Gly status) show a diminished peak response to inhaled salbutamol in comparison to children with wheeze carrying the Gly/Gly status.

The sample size calculations are based on data published by Beydon et al. [9]. Mean baseline Rint in asthmatic children was 0.92, SD 0.22 kPa/L/s; levels dropped to 0.74, SD 0.18 kPa/L/s after bronchodilator administration. In children who did not have asthma, the baseline Rint dropped by a smaller proportion, decreasing 0.10 unit to 0.82 kPa/L/s. All the children in this study will have wheeze. Hence, we feel they will have a higher baseline airway resistance comparable to children with asthma, and higher than controls without asthma, as reported in [9]. However, we estimate that children carrying one or both copies of Arg will show a diminished response that is comparable to that of children who do not have asthma. Thus our sample size calculations are based on the prediction that the peak bronchodilator response in the children who have Arg/Arg or Arg/Gly status will show a mean fall in Rint of 0.10 unit to 0.82 kPa/L/s, whereas the wheezy children who have Gly/Gly status will show a response that is at least as substantial as that observed by Beydon et al. [9] in children with asthma (i.e. a mean fall of 0.18 kPa/L/s).

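### The research question 1 sample size assumes a gap between two active doses (0.23) larger than the whole bronchodilator response the protocol quotes from the same source (0.18)

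*Protocol article*

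**What the plan says.** All statements are in the protocol article.

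- **Sample size, justification for research question 1.** The planned comparison is of changes from baseline across doses: "We plan to compare the difference in change from baseline between different salbutamol doses". The effect is introduced with "we would define the minimum clinically important difference (MCID) for paired" and given in "tests as mean −0.23, standard deviation (SD) 0.19". No unit is printed. The authors "set the threshold of significance at 0.01 to account for multiple" t tests. The effect is then applied to a contrast between doses, "In order to detect a worthwhile difference of this size between dosages", and the result is "with 90 % power, a minimum of 24 patients will be needed in each dosage group, giving a sample size of 96 patients".
- **Sample size, justification for research question 2.** From the same cited study, asthmatic children start at 0.92 (SD 0.22) kPa/L/s and "levels dropped to 0.74, SD 0.18 kPa/L/s after bronchodilator administration". The protocol restates this as "a mean fall of 0.18 kPa/L/s". It then assumes a baseline/post-dose correlation of 0.6, arrives at 136 children, and inflates this to 156 for failed measurements.
- **Dosage schedules.** All four arms receive salbutamol. Each child has Rint measured at baseline and after each of two cumulative doses.
- **Statistical analysis plan section.** Post-bronchodilator Rint is regressed on baseline, with the 100 + 300 schedule as reference, 99% confidence intervals and a 0.01 significance threshold. This is a comparison between randomised groups.

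**The concern.** A minimum important difference labelled for a paired test describes a change within a child. The same number is then used as the difference between two doses, both active. That difference is normally only a part of the full response to the drug, yet here it is larger than the full mean response quoted in the next paragraph from the same study.

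What is at stake is how the dose comparison will be read. The Background raises the possibility that a small dose is adequate for most children, in which case larger ones should not be prescribed. If readers believe the trial had 90% power for a worthwhile difference between doses, they may take a non-significant contrast as evidence that doses perform alike. The stated power does not support that reading for differences well below the full response.

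**Working it through.** **Inputs.** Research question 1: difference 0.23, SD 0.19, alpha 0.01, power 90%, 24 per group. Research question 2: baseline 0.92 (SD 0.22), post-dose 0.74 (SD 0.18), correlation 0.6, 136 evaluable, so 136/4 = 34 per group. Assumptions: two-sided testing (sidedness is not stated), and kPa/L/s as the unit of 0.23, taken from the research question 2 paragraph.

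**1. Reproduce the plan's figure.** Power comes from the noncentral t distribution.

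- Independent groups: noncentrality = δ / (SD × √(2/n)), df = 2n − 2.
- Paired: noncentrality = δ × √n / SD, df = n − 1.

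| Calculation (δ 0.23, SD 0.19, two-sided 0.01) | n | Power |
|---|---|---|
| Independent, per group | 22 | 89.9% |
| Independent, per group | 23 | 91.5% |
| Independent, per group | 24 | 92.8% |
| Paired | 13 | 87.8% |
| Paired | 14 | 91.2% |
| Paired | 24 | 99.8% |

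The stated 24 is within one of the independent-groups answer (23) and far from the paired answer (14). A normal approximation gives 21 per group and a one-sided two-sample t test gives 20. So 0.23 was evidently used as a difference between groups, which also matches the planned regression. The arithmetic is sound; the input is the problem.

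**2. Compare the input with the quoted response.** 0.92 − 0.74 = 0.18, and 0.23 / 0.18 = 1.28.

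**3. Is 0.19 a within-child SD?** The SD of change implied by the research question 2 figures is √(0.22² + 0.18² − 2 × 0.6 × 0.22 × 0.18) = 0.182, close to 0.19. With the paired label, this suggests, but does not prove, that a within-child change was reused as a between-dose difference.

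**4. What 34 per group deliver (two-sided alpha 0.01).** Two SDs bracket the range: 0.19 unadjusted, and 0.18 × √(1 − 0.6²) = 0.18 × 0.8 = 0.144 after regression on baseline. The half-width of the 99% interval is t(0.995, 66 df) × SD × √(2/34) = 2.652 × SD × 0.2425.

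| | SD 0.144 | SD 0.19 |
|---|---|---|
| Detectable difference, 90% power | 0.138 | 0.182 |
| As a share of 0.18 | 77% | 101% |
| 99% CI half-width | 0.093 | 0.122 |
| Power for 0.18 | 99% | 89% |
| Power for 0.09 (half the response; illustration) | 47% | 25% |
| Power for 0.08 (illustration) | 37% | 19% |

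The last two rows are illustrations only, because the protocol names no other target difference between doses. The 0.08 is the genotype difference used for research question 2.

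**The case against.** **Origin and unit of −0.23.** The cited study is not at hand and no unit is printed, so the number may be a subgroup result or a cut-off for individual response. This stands as a limit on what can be said: the two figures are unreconciled, and 0.23 is not shown to be a transcription error. A cut-off for one child's change would still need an argument before serving as a mean difference between doses.

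**0.18 is not a ceiling.** The protocol expects Gly/Gly children to respond at least that strongly. It does not say what bronchodilator dose lay behind the 0.18, and the trial goes up to 800 μg. This also stands. A reader might infer that a 0.23 gap is impossible, since one dose would have to worsen Rint, or that the 90% power applies to no difference the trial could ever observe. One quoted mean does not support either statement; it supports implausible on the protocol's own figures.

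**A paired comparison exists in this design.** Each child is measured after two cumulative doses, so a within-child dose contrast is possible. That is true, but neither the stated 24 nor the planned regression corresponds to it.

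**The trial recruits 156, not 96.** Correct, and 34 per group have 89% to 99% power for a difference of 0.18. This softens the shortfall without making 0.23 a sensible target.

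**No smaller dose difference is declared relevant.** Also correct. A reader might take 0.08 from research question 2 as a meaningful dose difference and conclude that relevant effects would usually be missed. The protocol uses 0.08 only for genotype, so that conclusion does not follow.

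**Conclusion.** The point holds as an inconsistency of assumption, not of arithmetic. The stated 90% power is tied to a difference between two active doses of about 128% of the full mean response quoted from the same source, and the test named is not the one that yields 24 per group. On the protocol's own inputs, 34 evaluable children per group have 90% power only for differences of about 0.14 to 0.18, which is 77% to about 100% of that response.

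This rests on two-sided testing, kPa/L/s as the unit of 0.23, SDs from 0.144 to 0.19, and all 136 children being evaluable. It does not show that the trial is too small for a dose difference the investigators have declared important, because apart from 0.23 they have declared none.

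**What to change.** Rewrite the research question 1 sample size paragraph:

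1. Reconcile 0.23 with 0.18: give its unit, what it measures in the cited study, and why it is a credible difference between doses. Otherwise remove it as the between-dose target.
2. State that the contrast being sized is the between-group one in the planned regression. If a within-child contrast is intended, justify it and size it as such.
3. Replace the 90% power statement with what 34 evaluable children per group provide at two-sided alpha 0.01: a detectable difference of about 0.14 to 0.18 at 90% power, and an expected 99% confidence interval half-width of about 0.09 to 0.12. Label power for any smaller difference as an illustration.

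The cost is one paragraph and a less favourable stated figure. The recruitment target stays at 156, since research question 2 sets it. Recasting research question 1 as an estimation objective, or pooling the two schedules that end at 400 μg, is optional and not needed to correct the text.

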### Justification for research question 2: Arg versus Gly beta agonist response

Can we predict the salbutamol dose that is appropriate for an individual child using simple, non-invasive and inexpensive tests that can be performed in the outpatient setting?

The hypothesis to be tested is that children with wheeze who are either homozygous or heterozygous for arginine at position 16 of the beta2 receptor (i.e. Arg/Arg or Arg/Gly status) show a diminished peak response to inhaled salbutamol in comparison to children with wheeze carrying the Gly/Gly status.

The sample size calculations are based on data published by Beydon et al. [9]. Mean baseline Rint in asthmatic children was 0.92, SD 0.22 kPa/L/s; levels dropped to 0.74, SD 0.18 kPa/L/s after bronchodilator administration. In children who did not have asthma, the baseline Rint dropped by a smaller proportion, decreasing 0.10 unit to 0.82 kPa/L/s. All the children in this study will have wheeze. Hence, we feel they will have a higher baseline airway resistance comparable to children with asthma, and higher than controls without asthma, as reported in [9]. However, we estimate that children carrying one or both copies of Arg will show a diminished response that is comparable to that of children who do not have asthma. Thus our sample size calculations are based on the prediction that the peak bronchodilator response in the children who have Arg/Arg or Arg/Gly status will show a mean fall in Rint of 0.10 unit to 0.82 kPa/L/s, whereas the wheezy children who have Gly/Gly status will show a response that is at least as substantial as that observed by Beydon et al. [9] in children with asthma (i.e. a mean fall of 0.18 kPa/L/s).

The ratio of children carrying Arg/Arg and Arg/Gly status to those with Gly/Gly is 60 %:40 %. A sample size of 133 (80 Arg and 53 Gly/Gly) would allow us to detect a difference of 0.08 unit between the groups (delta = 0.08, SD = 0.20; effect size = 0.4) with 80% power for 5% significance, assuming a correlation between baseline and post-bronchodilator measurements of 0.6. To allow randomisation of equal numbers to the four groups, the sample size should be increased to 136. In order to allow a sample size sufficiently large to answer both research questions, and to allow for up to 12 % of children being unable to perform the measurement (based on experience in our unit in this age range), we will recruit a sample size of 156 children. We intend to recruit these children over 36 months.

### Study of the relationship between urinary salbutamol levels and Rint measurements

The concentration of salbutamol in the urine at 30 min following a dose of salbutamol represents the gold standard of lung bioavailability. This has been established in adults. We will try to collect as many urine samples as possible, and we will aim to study the dose that is available to the lungs, measured as the 30 min urine salbutamol, against bronchodilator response. Data analysis will be performed as discussed above for inhaled lung dose versus bronchodilator response. As the production of urine on request is rather uncertain in children of this age, this is intended as a distinct secondary analysis. The main project, including the principal outcomes, will not be affected in any manner if the collection of these samples is incomplete.

## Assignment of interventions

Participants will be randomised to the various pairs of salbutamol doses by a member of the research team using a web-based system (http://www.sealedenvelope.com/). Those delegated the role of randomising participants will be assigned a sealed.envelope.com randomisation user name and password by the trial manager. To randomise a participant, the randomiser will follow the OpSal Randomisation Guide. The randomisation system will be accessed at the following website: https://www.sealedenvelope.com/bsuh/users.

At the point of consent, a participant identifier will be assigned to the patient using the Participant Number Assignment Log. To randomise a participant, the participant identifier and date of birth must be entered, and then the inclusion and exclusion criteria must be confirmed. The participant is then randomised to a dosage schedule. An email notification is then sent to the randomiser and the coordinating centre.

An allocation sequence has been generated with four possible dosage schedules on a 1:1:1:1 basis. There is no stratification. The randomisation code list was generated by the trial statistician, and it was uploaded onto the web-based system by the trial manager. The direct research team members do not have access to the randomisation code list; therefore, concealment of allocation sequence is maintained until the moment of assignment.

The researcher performing the Rint measurement on the participant will be blinded to the dosing schedule until after the assessment has been performed. Two members of the research team will be required for the study visit. Researcher 1 will perform the Rint measurements and will be blinded to the dosage schedule. This researcher must leave the room whilst the salbutamol is being administered to the participant and any associated paper work must be concealed from this researcher until the study assessments have been performed. Researcher 2 will be unblinded to the dosage schedule. Researcher 2 will randomise the participant using the web-based randomisation service (sealedenvelope.com) on the day of the visit and will then administer the salbutamol. Once the final Rint measurement has been performed, the dosage schedule can be revealed to members of the research team if necessary.

In the unlikely event that the blinded researcher needs to know the dosage schedule given to the participant and unblinded members of the research team are not available to disclose it, the dosage schedule for each participant will be documented in the Case Report Form (CRF) and filed in the site file. The sponsor will also retain a copy of the randomisation list and will be notified of the dosage schedule at the point of randomisation via sealed.envelope.com.

## Data collection, management and analysis

### Data collection methods

The majority of data collected for the study will be recorded directly into the paper CRF. Source data entered directly into the CRF will include:Clinical history with a focus on wheeze and related atopic diseasesRecent medication in relation to wheezeStudy procedures: salbutamol dosing schedule, Rint measurements, saliva and urine sampling

The following information must be recorded in the participant’s health records in addition to the CRF:EligibilityInformed consentTrial numberAdverse events and any other clinically significant informationWithdrawal from the trial where appropriate

A copy of the original CRF should be kept in the participant’s health records. The CRF will be faxed or emailed to the Brighton and Sussex Clinical Trials Unit, Brighton, as per the study-specific CRF completion guidelines held in the site file. The original CRF will be stored in the site file.

Blank and completed copies of the paper CRF will be stored securely in the site file. Any deviations from the protocol will be noted on the CRF and documented in the Protocol Deviation Log stored in the site file.

The information collected during the study, including the genetic information, will be stored on a database. The information will be used solely for the purpose of research into childhood diseases related to inflammation. This may include sharing anonymised data from the study with researchers in France and Italy. Explicit consent from the parent will be obtained for this.

## Safety reporting (ICH Guideline E2A 1994)

An adverse event (AE) is defined as any unfavourable and unintended sign, symptom or disease temporally associated with the use of an investigational medicinal product or other protocol mandated intervention.

An adverse reaction (AR) is any untoward and unintended response to an investigational medicinal product related to any dose administered. All AEs judged by either the reporting investigator or the sponsor as having reasonable causal relationship to a medicinal product qualify as adverse reactions. The expression ‘reasonable causal relationship’ means to convey in general that there is evidence or argument to suggest a causal relationship (possible, probable or definite).

A serious adverse event (SAE) is any AE regardless of causality that:Results in death (during treatment with, and for 30 days after stopping, study drug).Is life-threatening, meaning that the patient was at immediate risk of death from the reaction as it occurred; i.e. it does not include a reaction which hypothetically might have caused death had it occurred in a more severe form.Requires hospitalisation or prolongs existing hospitalisation. Admissions and/or surgical operations scheduled to occur during the study period but planned prior to study entry or elective operations are not considered AEs if the illness or disease existed before the patient was enrolled in the trial, provided that it did not deteriorate in an unexpected manner during the trial (e.g. surgery performed earlier than planned).Results in persistent or significant disability or incapacity.Is a congenital anomaly/birth defect.Requires medical intervention to prevent permanent damage, or another medically important event, defined as an event that may not result in death, be life-threatening or require hospitalisation but may be considered an SAE when, based upon appropriate medical judgment, it may jeopardize the patient or subject and may require medical or surgical intervention to prevent one of the outcomes listed in the definitions for SAEs.

A serious adverse reaction (SAR) is defined as an SAE that has a definite, probable or possible causal relationship to the study drug (salbutamol). An adverse reaction is ‘unexpected’ if its nature and severity are not consistent with the information about the medicinal product set out in the Summary of Product Characteristics (SmPC). A suspected unexpected serious adverse reaction (SUSAR) is a drug-related SAR that has not previously been reported as a drug-related SAR (i.e. is not listed in the SmPC). Table 3 is taken from the salbutamol SmPC and lists the adverse events expected when taking salbutamol. This table should be referred to when determining the expectedness of an event. Frequencies are defined as: very common (≥1/10), common (≥1/100 and <1/10), uncommon (≥1/1000 and <1/100), rare (≥1/10,000 and <1/1000), very rare (<1/10,000) and not known (cannot be estimated from available data).

**Table 3 Tab3:** Adverse events expected when taking salbutamol, taken from the SmPC

Adverse event	Common	Uncommon	Rare	Very rare
Immune system disorders		Hypersensitivity reactions (angio-oedema, urticaria, hypotension and collapse)		
Metabolism and nutrition disorders			Hypokalaemia	
Nervous system disorders		Headache	Hyperactivity, restlessness, dizziness	
Cardiac disorders	Palpitations			Myocardial ischaemia, cardiac arrhythmias including atrial fibrilation, supraventricular tachycardia and extrasystoles
Vascular disorders	Peripheral vasodilatation, and as a result small increase in heart rate			
Respiratory, thoracic and mediastinal disorders			Bronchospasm, cough, irritation of mouth and throat which may be prevented by rinsing the mouth after inhalation	
Musculoskeletal and connective tissue and bone disorders	Tremor		Muscle cramps	

All AEs will be documented in the hospital notes. ARs will be recorded in the hospital notes and in the CRF which will be filed in the participant’s hospital records. SAEs and SARs will be recorded in the hospital notes and the CRF and will be reported to the sponsor in an expedited fashion as per the relevant sponsor Standard Operating Procedure (SOP) for Safety Reporting. Whether expected or not, Table 4 illustrates how the events should be reported during the study. For each event the investigator or other medically qualified doctor on the delegation log will make a documented assessment of causality, seriousness and expectedness. If the research team becomes aware of any SARs once participation has stopped, these will be reported to the sponsor in an expedited fashion as per the relevant sponsor SOP for Safety Reporting.

**Table 4 Tab4:** Procedure for reporting adverse events during the trial

Type of event^a^	Hospital notes	CRF	Expedited reporting (immediately and within 24 h)
Adverse event	Yes	No	No
Adverse reaction	Yes	Yes	No
Serious adverse event	Yes	Yes	Yes
Serious adverse reaction	Yes	Yes	Yes

^a^For definitions see section on Safety reporting (ICH Guideline E2A 1994) in main text

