Thus there is now the possibility of correlating inhaled salbutamol dose with clinical response (measured as change in Rint) in younger children in the age range 2 years 6 months to 6 years 11 months. It is therefore of importance to document the airway response to increasing doses of inhaled salbutamol in this age group. To do this we need to document airway response against 30-min urinary salbutamol, the best available estimate for the bioavailability of salbutamol in the lungs. With expert children’s nurse support, we believe that most young children can be persuaded to pass a sample of urine at about 30 min following inhalation. However, we cannot assume that this will happen in all children and have made this a secondary outcome of the trial.

The proposed work is likely to identify a population of children who do not show a satisfactory response to salbutamol. There is evidence from studies in older children and young adults that one reason for this poor response may be a genetic change in their beta2 receptor (Arg/Gly16) [7, 8]. The presence of this polymorphism can be identified by DNA analysis on a simple saliva sample, without the need for specialist pulmonary function equipment. As these samples can easily be obtained in primary care, we propose to investigate whether this polymorphism is an effective marker for poor salbutamol efficacy in these younger children.

Overall, the proposed research will exploit simple, non-invasive and inexpensive tests that can mostly be performed in an outpatient setting in order to help develop the evidence for the correct dose of salbutamol in younger children with recurrent wheeze who have been prescribed salbutamol by their doctor. It is possible that a small dose of salbutamol, such as 2 puffs (200 μg) is adequate for most of these children. If this is the case, larger doses, such as 1000 μg, should not be prescribed (as is current practice) as they may induce side effects in these children. Secondly, some younger children who are currently prescribed larger doses of salbutamol may in fact be ‘poor responders’ or ‘non-responders’ to salbutamol due to their genetic constitution. Such children may benefit from alternative ‘reliever’ medicines, such as ipratropium or montelukast.

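### The protocol both requires adverse events in the CRF and, in Table 4, keeps plain adverse events out of it, so non-serious events judged unrelated may not reach the trial data

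*Protocol article*

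**What the plan says.** Two sections of the protocol article say where an adverse event is recorded.

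- **Data collection methods.** A list of items "must be recorded in the participant’s health records in addition to the CRF". Adverse events are on the list, without restriction to related or serious ones. The same section gives the route of the data: "The CRF will be faxed or emailed to the Brighton and Sussex Clinical Trials Unit".
- **Safety reporting (ICH Guideline E2A 1994), text.** "All AEs will be documented in the hospital notes. ARs will be recorded in the hospital notes and in the CRF".
- **Safety reporting, Table 4** (columns: hospital notes, CRF, expedited reporting). The rows read "Adverse event Yes No No", "Adverse reaction Yes Yes No" and "Serious adverse event Yes Yes Yes". The row for serious adverse reactions has the same entries as that for serious adverse events.

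The step from adverse event to adverse reaction is a judgement: "All AEs judged by either the reporting investigator or the sponsor as having reasonable causal relationship to a medicinal product qualify as adverse reactions". A link rated merely possible is sufficient.

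Table 2 schedules adverse events as an assessment at both doses. The Background argues that, if a small dose is adequate, larger ones should not be prescribed "as they may induce side effects in these children".

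**The concern.** The two sections give opposite instructions for a plain adverse event. The text and Table 4 under Safety reporting agree with each other; the conflict is between them and Data collection methods.

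Side effects are part of the trial's rationale, and the Background says that they are hard to monitor at this age because young children often cannot report them. It also describes hyperactivity as little studied, though parents commonly report it with relatively large doses. In a wheezy child of this age, restlessness or cough could be put down to behaviour or to the underlying illness. Under Table 4, an event explained away like that stays in the hospital notes, for which no route to the trials unit is described.

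At stake is whether the safety data in the trial database are complete, or have been filtered by a causality opinion formed event by event. In a randomised comparison, the usual protection is to count every event whatever its presumed cause, so that the opinion cannot differ between arms.

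**Working it through.** No sample size, power or event figure is involved, so the check is a comparison of the instructions by event type.

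| Event type | CRF under Data collection methods | CRF under Table 4 | Agree? |
|---|---|---|---|
| Non-serious, judged not even possibly related | Yes | No | **No** |
| Adverse reaction (link at least possible), non-serious | Yes | Yes | Yes |
| Serious adverse event, any causality | Yes | Yes | Yes |
| Serious adverse reaction | Yes | Yes | Yes |

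1. **Extent of the conflict.** One of the four categories is affected. The definition of a serious adverse event applies regardless of causality, so no serious event is lost. An event with a possible link is an adverse reaction and is not lost either.

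2. **What decides whether a non-serious event is in the CRF.** Under Data collection methods, its occurrence is enough. Under Table 4, the investigator or the sponsor must also judge a link at least possible. A plain adverse event is neither entered in the CRF nor expedited, so no reporting route is stated by which the sponsor would see it and make its own judgement.

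3. **Who judges, and knowing what.** Safety reporting assigns causality to the investigator or another medically qualified doctor on the delegation log. That person is not stated to be blinded to dose. Assignment of interventions blinds the researcher who measures Rint, lets the schedule be revealed once the last Rint measurement is done, and has the schedule documented in the CRF. A judgement made with knowledge of the dose is therefore possible. The document does not say that it happens.

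4. **What can be recovered.** All adverse events must be in the hospital notes, and each event needs a documented assessment of causality, seriousness and expectedness. The information exists whichever instruction is followed.

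5. **Children concerned.** The target is 156 children, with 37 recruited as of June 2016. That leaves 156 − 37 = 119 for whom a corrected rule could apply from the start, and 37 whose notes would need checking. The number of affected events cannot be derived.

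**The case against.** The strongest reply is that little is lost. The threshold for an adverse reaction is low, and Table 3 already names palpitations, tremor, hyperactivity and restlessness as expected effects of salbutamol, so an assessor is prompted to consider a link. Serious events are always captured. Safety by dose is not a stated endpoint or analysis: the statistical analysis section covers Rint by dosage regimen and by genotype. The protocol also justifies light safety oversight by the drug's well-researched safety profile. All of this stands, and it limits the point to a reconciliation.

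Four stronger readings are tempting, and the document does not support them.

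- A reader might infer that the database would hold only events caused by salbutamol. It would also hold serious events of any cause, and events whose link is only possible.
- A reader might infer that the unblinded Researcher 2 judges causality. That role is described as randomising the child and giving the drug. All that can be said is that blinding of the causality assessor is not stated.
- A reader might infer that a planned comparison of side effects by dose is compromised. The article states no such comparison, and tabulation of adverse events is commonly left to an analysis plan that is not shown.
- A reader might infer that correcting Table 4 would widen the quarterly safety review. By its own wording, that review covers adverse reactions and serious events, and it would still do so.

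The reply does not remove the contradiction. Staff completing the CRF have two current instructions for the same event, and only one of them makes inclusion independent of a causality opinion.

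**Conclusion.** The contradiction is real but narrow. Data collection methods and Table 4 disagree on one category: non-serious adverse events judged not even possibly related to salbutamol. If Table 4 is followed, these events are absent from the CRF, and any description of side effects by schedule drawn from CRF data rests on judgements not stated to be blinded. The size of any resulting distortion is unknown, and nothing in the document allows an estimate.

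The conclusion assumes that the list under Data collection methods means what it literally says, namely both records for every adverse event, and that the CRF is the only route to the trials unit, since no other is described. The primary Rint analysis and the genotype analysis are unaffected. The point is worth correcting because the remedy is nearly free and removes an avoidable filter in an age group where side effects are admittedly hard to ascertain.

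**What to change.** Reconcile the two sections so that every adverse event is entered in the CRF:

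- In Table 4, change the CRF entry in the adverse event row from No to Yes, and align the sentence above the table.
- Record each event's timing relative to dose 1 or dose 2. Each child receives two successive doses, so the schedule alone does not show the cumulative dose received when the event occurred.
- For children already recruited (37 as of June 2016), transcribe adverse events from the hospital notes into the CRF.

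The cost is a small amount of extra data entry and a one-off transcription from notes that must already exist. No assessment is added for the child, because Table 2 already schedules adverse events at both doses.
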